### Design

This study will be a randomised, assessor- and statistician-blinded, placebo-controlled trial. A total of 36 subjects with PDM who meet the guidelines of the Society of Obstetricians and Gynaecologists of Canada for the diagnosis of PDM will be recruited and randomly assigned to a shock wave group or a sham shock wave group at a 1:1 ratio. Table 1 lists the recruitment process, intervention methods and evaluation, and Fig. 1 depicts the experimental flow chart. The Standard Protocol Items: Recommendations for Interventional Trials (SPIRIT) 2013 checklist is attached as Additional file 1. This study commenced in January 2019 at the Zhongshan-Xuhui Hospital, Fudan University, Shanghai, China.

**Table 1 Tab1:** Study design schedule

Period	Screening	MRI scan	Treatment	MRI scan	Close-out
Menstrual cycle	0 month	1 month	1 month	1 month	1 month
Inclusion and exclusion criteria	√				
Informed consent	√				
Physical examination	√				
Medical history	√				
Comorbidities	√				
Pelvic MRI	√				
Allocation			√		
SF-MPQ		√		√	
CMSS		√		√	
SAS and SDS		√		√	
Patient compliance					√
Reasons for dropout or withdrawals					√
Adverse events					√
Safety evaluation					√

*CMSS* COX Menstrual Symptom Scale, *MRI* magnetic resonance imaging, *SAS* Zung Self-rating Anxiety Scale, *SDS* Self-rating Depression Scale, *SF-MPQ* Short form of the McGill Pain Questionnaire

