### Outcome measurements

#### Primary outcomes

##### SF-MPQ

The primary outcome will be the change in the short form of the McGill Pain Questionnaire (SF-MPQ) score (Table 1). The SF-MPQ is a scale composed of a pain rating index, a visual analogue scale and existing pain intensity to measure pain intensity. The pain rating index consists of 11 sensory and 4 emotional pain descriptors, all of which are rated from 0 to 3 points to indicate the different degrees of no, mild, medium, or severe pain, respectively. This index is a sensitive and reliable pain evaluation method widely used in the assessment of dysmenorrhoea [18].

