##### CMSS

The menstrual pain symptoms of participants will be integrally evaluated by the Cox Menstrual Symptom Scale (CMSS), which consists of 18 items or symptoms, including cramps, nausea, vomiting, loss of appetite, headaches, backaches, leg aches, dizziness, weakness, diarrhoea, facial blemishes, abdominal pain, flushing, sleeplessness, general aching, depression, irritability, and nervousness [19]. The scale is mainly used to evaluate the severity and duration of menstrual pain symptoms. All items use a five-level scoring method ranging from 0 to 4 points. The choices for pain severity include painless, mild pain, moderate pain, severe pain, and very serious pain. Patients can evaluate the duration of their pain as 0 h, less than 3 h, 3–7 h, 7–24 h and more than 24 h. The CMSS will be used before and after rESWT treatment.

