### Statistical analysis

Clinical and MRI outcomes will be obtained in this study. Among these outcomes, results from participants for both MRI scans and two clinical evaluations will be included in the results analysis; otherwise they will be considered data from drop-outs. Note that all participants in the experiment will receive our instructions before participating.

Statistical analysis of the clinical outcomes will be accomplished using the SPSS 22.0 statistical software. All tests will be bilateral, and *p* < 0.05 will be considered statistically significant.

Demographic characteristics and baseline information for all participants will be analysed statistically. For continuous data, independent sample *t* tests or Wilcoxon rank sum tests will be applied for analysis with data represented as mean ± standard deviation. If dichotomous data occur, we will use the chi-square test or the Friedman test and represent the data as percentiles.

For post-test results, the paired *t* test or Wilcoxon signed rank test will be employed for continuous data within the group. Conversely, the chi-square test or Fisher’s exact test will be applied for two-part data to compare the differences before and after treatment. For different intervention methods, independent sample *t* tests will be conducted to identify whether the intervention methods show differences for the relief of PDM.

The statistical comparison of MRI data will be conducted in different ways. With the use of the 3.0 T Siemens Magnetom Verio MRI system, each subject will produce two resting state scans. The data processing assistant for resting state fMRI (DPARSF 4.4) software package will be used to process MRI data on the MATLAB 2015b platform and obtain the ALFF values. The mean value of the amplitude of all frequency points within 0.01–0.08 Hz will be calculated; that is, the intensity of the BOLD signal changes will be calculated to obtain the brain map of the statistical parameter of amplitude, which will be used to describe the spontaneous activity of the voxel [23]. SPM12 software will be employed to perform two-sample *t* tests on the two groups of statistical brain maps. The final results will be superimposed on standard avg152 T1 images for display. Finally, the statistical difference of low-frequency amplitudes in the resting state between the two groups will be obtained, and *p* < 0.05 will be considered to indicate a significant statistical difference.

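### The between-group t test is valid but less precise than ANCOVA on the baseline scores already collected, and two stated rules for binary data (unpaired tests before/after, Friedman at baseline) name the wrong method

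*Protocol article*

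**What the plan says.** All of this is in the protocol article.

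- **Between groups, clinical scores (Statistical analysis).** Independent-sample t "tests will be conducted to identify whether the intervention methods show differences for the relief of PDM". This is the only between-group rule given for post-treatment clinical scores, and no covariate is mentioned. Tests are two-sided ("All tests will be bilateral, and" significance is set at p < 0.05).
- **What is measured.** "The primary outcome will be the change in the short form of the McGill Pain Questionnaire (SF-MPQ) score" (SF-MPQ). "The CMSS will be used before and after rESWT treatment" (CMSS). The SAS and SDS sections say the same of those scales. Table 1 ("Study design schedule") ticks all four scales at the MRI visit before treatment and again at the MRI visit after it. Allocation is ticked in the treatment column between them.
- **Within group, continuous data (Statistical analysis).** The paired t "test or Wilcoxon signed rank test will be employed for continuous data within the group".
- **Before/after, binary data (Statistical analysis).** Chi-square or Fisher's "exact test will be applied for two-part data to compare the differences before and after treatment".
- **Baseline, dichotomous data (Statistical analysis).** If such data occur, "we will use the chi-square test or the Friedman test and represent the data as percentiles".

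**The concern.** Three separate matters sit in the same section.

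1. A baseline value of every clinical scale is collected, and only participants with both evaluations are analysed, so the covariate is available for everyone in the analysis. The efficacy test does not adjust for it. In a trial planned on 15 evaluable participants per group, that precision is worth having. For CMSS, SAS and SDS the section does not say whether the t test is run on the change or on the post-treatment score.
2. Before and after values of a binary variable come from the same person. Chi-square and Fisher's exact test on the before-by-after margins assume two independent samples. The plan pairs its continuous within-group tests correctly but not its binary ones.
3. The Friedman test ranks repeated measurements within blocks. It has no application to one dichotomous variable compared between two independent arms.

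At stake are a wider confidence interval than necessary for the efficacy result, and p-values from the wrong reference distribution for any binary variable that is analysed.

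**Working it through.** **Inputs.** Evaluable size is 15 per group (Sample size calculation), enrolled size 18 per group. The article gives no standard deviation, mean difference or pre-post correlation for any scale, so there is no plan figure to reproduce here. The pre-post correlation r is an assumption, shown at 0.3, 0.5 and 0.7. The within-person correlation phi of a binary variable is an assumption, shown from 0 to 0.7.

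**Part 1: precision of the between-group test.** Take equal variance before and after, scaled to 1. The variance of the estimated group difference is proportional to:

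- change score: 2(1 − r)
- post score only: 1
- ANCOVA, large sample: 1 − r²

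Estimating the slope adds a factor 1 + 1/(2n − 4) for a normal covariate. At n = 15 this is 27/26 = 1.038.

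| r | change ÷ ANCOVA, large sample = 2/(1 + r) | same at 15 per group (÷ 1.038) | post-only ÷ ANCOVA, large sample = 1/(1 − r²) | same at 15 per group (÷ 1.038) |
|---|---|---|---|---|
| 0.3 | 1.54 | 1.48 | 1.10 | 1.06 |
| 0.5 | 1.33 | 1.28 | 1.33 | 1.28 |
| 0.7 | 1.18 | 1.13 | 1.96 | 1.89 |

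Each entry is the factor by which the t test's sample size would have to grow to match ANCOVA. Simulation at 15 per group (40,000 runs) agrees to within about 0.02.

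The gain has limits. Against the change score it vanishes when 2/(1 + r) = 1.038, that is r ≈ 0.93. Against the post score it vanishes when 1 − r² = 1/1.038 = 0.963, that is r ≈ 0.19.

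**Part 2: unpaired test on paired binary data.** Under no change with margin p, the difference of the before and after proportions has variance 2p(1 − p)(1 − phi)/n. The unpaired chi-square uses 2p(1 − p)/n. Its z statistic is therefore too small by √(1 − phi), and a nominal 5% test rejects with large-sample probability P(|Z| > 1.96/√(1 − phi)). At phi = 0.5 the threshold is 1.96/0.707 = 2.77, giving about 0.6%.

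Simulated null rejection with 18 pairs and margin 0.5 (20,000 runs):

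| phi | chi-square, uncorrected | Fisher | exact McNemar |
|---|---|---|---|
| 0 | 6.6% | 2.9% | 2.3% |
| 0.3 | 2.6% | 0.8% | 1.3% |
| 0.5 | 1.0% | 0.2% | 0.7% |
| 0.7 | 0.1% | 0.02% | 0.1% |

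Exact McNemar is itself conservative at this size because few pairs are discordant. The reason to use it is that it answers the paired question with the right reference distribution; the table does not show that it gains power over chi-square.

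Individual data sets can differ in either direction. With 15 pairs, 12 positive before and 6 after, the unpaired tests see only the margins: chi-square p = 0.025, Fisher p = 0.060. If 6 improved and none worsened, exact McNemar gives 0.031. If 7 improved and 1 worsened, it gives 0.070. The unpaired tests cannot tell these two data sets apart.

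**Part 3: Friedman.** No arithmetic is needed. The rule sits with the description of baseline characteristics by arm, where each participant contributes one value and there are no repeated measurements to rank.

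**The case against.** The strongest reply is that the t test is not an error. The SF-MPQ section defines the primary outcome as a change, so each participant's baseline already enters the analysis. Under randomisation a t test on change is unbiased and controls its type I error, and a condensed article often leaves covariate adjustment to the analysis plan. All of this stands except the last step: the article does not leave the comparison open but names the test. A reader might infer that the efficacy analysis ignores baseline, or is biased by chance imbalance. The documents do not support that for SF-MPQ; for the other three scales the analysed variable is simply unstated.

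On the binary rules, the reply is that they reach nothing that matters. The four scales are analysed as scores, no responder endpoint is defined among the outcomes, the Friedman sentence is conditional and concerns baseline description, and before/after tests are not the randomised comparison. This also stands. The sample size does rest on effectiveness proportions, so a binary analysis is foreseeable, but none is specified.

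A reader might also infer that the plan's within-group p-values are wrong in general, or that the unpaired tests would create false evidence of efficacy. Neither follows. Continuous within-group data get correctly paired tests, and under positive within-person correlation the unpaired binary tests reject too seldom rather than too often.

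**Conclusion.** The point holds, in three parts of unequal weight.

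- **Between-group test.** Valid, but less precise than ANCOVA. The gain over a change-score t test at 15 per group is about 1.48, 1.28 or 1.13 times the sample size at r = 0.3, 0.5 or 0.7. It rests on the assumed r, on equal variances before and after, and on a roughly linear relation. This is inefficiency, not bias.
- **Before/after binary data.** A wrong method as stated. It is typically conservative: about 1% null rejection for chi-square at phi = 0.5 with 18 pairs, of which part is the discreteness that exact McNemar shares.
- **Friedman test for dichotomous baseline data.** A wrong method as stated, with no bearing on efficacy.

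Neither binary error affects a defined efficacy endpoint. The change is worth making because it is inexpensive and improves the main comparison; the trial's conclusions are not invalid without it.

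**What to change.** In the Statistical analysis section:

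1. Make the between-group analysis of SF-MPQ, CMSS, SAS and SDS an ANCOVA of the post-treatment score on group and the same score at baseline, reporting the adjusted difference with its 95% confidence interval. This also settles which variable is analysed for each scale.
2. Use the exact McNemar test for any before/after binary data.
3. Replace the Friedman test with Fisher's exact test for dichotomous data compared between arms.
4. State that within-group before/after tests are descriptive and that efficacy is claimed only from the between-group comparison.

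The cost is one degree of freedom in the ANCOVA and a few sentences of analysis wording. No further data, visits or participants are needed, since every analysed participant must already have both evaluations.

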### MRI data analysis

An fMRI data processing assistant based on statistical parameter mapping will be used to preprocess the original MRI data (DPARSF, http://rfmri.org/DPARSF) using MATLAB R2015b. After complete preprocessing, data processing and analysis of brain imaging of the amplitude of low-frequency fluctuation (ALFF) will be processed by the resting-state fMRI data analysis toolkit [22]. Afterwards, a comparison, correction and acquisition of the image will be executed via the Rest Slice Viewer software, and the final result will be presented in combination with the specific anatomical position of the corresponding area of MNI coordinates.

The results of fMRI will be interpreted by two different radiologists, and then the rehabilitation doctors will further analyse this in combination with clinical symptoms. Finally, the two doctors will reach a final interpretation through consultation.

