This study aims to explore the differences in pain intensity, anxiety, depression, mood and functional brain networks in patients with PDM after rESWT treatment. To accurately elucidate the effect of rESWT, we will compare the changes in MRI indexes in the rESWT group and a sham rESWT group and test whether the changes in pain condition are related to changes in brain function after rESWT treatment. Although previous studies have examined brain function in patients with nervous disorders and abnormal change due to PDM, they only explored the disease itself and did not examine the intervention [23, 25, 26]. To our knowledge, our research will be the first to use MRI to reflect divergence of efficacy of rESWT treatment for PDM and the related neural mechanisms through a randomised controlled trial. Existing research [26] shows that midbrain activity is closely related to the Cox retrospective symptom scale (RSS; *r* = 0.489), and the medial prefrontal cortex activity and RSS showed negative correlation (*r* = −0.580); the medial prefrontal cortex aims to reduce the activity of the brain’s pain-regulating system. Thus, the CMSS was chosen as one of the main outcome measures for this study. This scale is usually employed to evaluate dysmenorrhoea symptoms and to detect the severity of dysmenorrhoea.

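### The between-arm fMRI test is worded as a difference in level although the stated aim is change, and its whole-brain p < 0.05 rule has no defined correction

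*Protocol article*

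**What the plan says.** The last paragraph of Statistical analysis sets out the MRI comparison. It notes that "each subject will produce two resting state scans", defines the ALFF value at each voxel as the mean amplitude over 0.01–0.08 Hz, and continues: "SPM12 software will be employed to perform two-sample *t* tests on the two groups of statistical brain maps". The product of the test is that "the statistical difference of low-frequency amplitudes in the resting state between the two groups will be obtained", and a p value below "0.05 will be considered to indicate a significant statistical difference". The paragraph names no multiplicity method, cluster rule, mask or region of interest, and does not say which scan supplies the maps.

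Three other places bear on this:

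- **MRI data analysis** says that, after the ALFF step, "a comparison, correction and acquisition of the image will be executed via the Rest Slice Viewer software".
- **Discussion**, on the aim of the study: "we will compare the changes in MRI indexes in the rESWT group and a sham rESWT group". The limitations paragraph again puts the emphasis on comparing changes between the arms. It also expects the MRI results to identify treatment-specific pathways even where effects do not differ significantly.
- **Abstract** lists change on fMRI as a secondary indicator, and Statistical analysis admits to the results only participants with both scans and both clinical evaluations.

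**The concern.** The faults are distinct and have different consequences.

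**Contrast.** The aim is change from before to after treatment, compared between arms. The test as written compares amplitudes, with no subtraction, paired map, group-by-time term or baseline covariate. An analyst following that paragraph could run a post-treatment comparison that answers a different question, usually with less precision.

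**Threshold.** A whole-brain comparison has tens of thousands of voxels. A bare p < 0.05 means very different things depending on whether it is a voxel-level or a corrected level, and the text does not say which.

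Exploring the central mechanism by resting fMRI is one of only two objectives. Because the Discussion is ready to interpret MRI pathways even without a difference in effect, chance regions could be reported as mechanism when the clinical comparison is null.

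**Working it through.** The article states no fMRI error rate or fMRI power, so there is no figure of its own to reproduce.

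**A. Contrast: the places side by side**

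- Abstract and Discussion: the quantity compared between arms is a change.
- Statistical analysis, MRI paragraph: the quantity compared is an amplitude, which is a level. Its reference to BOLD signal change explains amplitude within a scan, not pre-to-post change.
- Statistical analysis, clinical paragraphs: paired pre-post tests are named. The MRI paragraph has no equivalent.
- Requiring both scans is an inclusion rule. It does not by itself put the first scan into the test.

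**B. What use of baseline is worth**

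Let r be the pre-post correlation at a voxel (assumed; not in the document), with equal variance at both scans. Relative to a post-only comparison, the variance is

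- change map: 2(1 − r)
- baseline-adjusted map: 1 − r² (large samples)

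| r (assumed) | change map | baseline-adjusted |
|---|---|---|
| 0.3 | 1.40 | 0.91 |
| 0.5 | 1.00 | 0.75 |
| 0.7 | 0.60 | 0.51 |
| 0.8 | 0.40 | 0.36 |

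Size of chance imbalance: with 15 per arm (the Sample size calculation figure before drop-out), the standard error of the baseline difference at a voxel is √(2/15) = 0.37 SD. With 18 per arm it is √(2/18) = 0.33 SD.

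**C. Number of tests**

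Inputs from MRI scanning procedure: field of view 192 × 192 mm, voxel 3 × 3 × 5 mm = 45 mm³, 28 slices. The same sentence gives a 1 mm slice thickness, which conflicts with the 5 mm voxel dimension; the stated voxel size is used here.

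- Grid: (192/3)² × 28 = 64 × 64 × 28 = 114,688 voxels.
- In-brain, assuming 1.2–1.6 L: 1,200,000/45 = 26,667 to 1,600,000/45 = 35,556.
- Results are to be reported in MNI coordinates, so maps will be resampled. At an assumed 3 mm (27 mm³): 44,444 to 59,259.

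**D. False positives if p < 0.05 is per voxel and uncorrected**

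- Expected false voxels under the null: 0.05 × 26,667 = 1,333 to 0.05 × 35,556 = 1,778. At 3 mm: 2,222 to 2,963.
- Neighbouring voxels are correlated, so the effective number of independent tests m is smaller. The chance of at least one false positive is 1 − 0.95^m: 0.951 at m = 59, 0.994 at m = 100, above 0.9999 at m = 200.
- Null simulation: two-sided tests (the clinical paragraph says "All tests will be bilateral"), 15 v 15 and 18 v 18, 52,304 in-mask 3 mm voxels, assumed smoothing of 4, 8 or 12 mm, 60 runs per setting. At least one false voxel appeared in every run of every setting. The mean was about 2,500–2,700 false voxels and, at 8 mm, about 80 false clusters of 10 or more voxels.
- A stricter uncorrected p < 0.001 also gave at least one false voxel in every run.

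**E. If the level is corrected**

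Bonferroni over 52,304 voxels (0.05/52,304 ≈ 9.6 × 10⁻⁷) gave any false voxel in about 0.02–0.08 of runs, against a nominal 0.05.

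**The case against.** The strongest reply has four parts.

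1. **Change maps would fit the words.** A two-sample t test can be run on post-minus-pre maps, both scans are required, and the Discussion speaks of changes. This stands. A reader might infer that the plan discards the baseline scan, but the article never says so. What it shows is a contrast that reads as a level, is left undefined, and disagrees with the stated aim.
2. **A correction step is mentioned.** It could mean multiplicity correction, and an article may leave the method to a fuller protocol or SAP that is not shown. This stands in part. A reader might infer that false regions are near certain under the plan; that follows only if p < 0.05 is uncorrected. Yet the article does state a decision rule, "0.05 will be considered to indicate a significant statistical difference", does not tie it to the correction, and does not say what the correction applies to.
3. **A post-only comparison is valid under randomisation.** Correct. A reader might infer that baseline differences will systematically appear as treatment effects, or that omitting baseline helps to produce the false regions. Neither follows: chance imbalance is already in the standard error, and the false-positive count comes from multiplicity alone.
4. **fMRI is secondary, and the trial calls itself exploratory.** Correct, and it limits the severity.

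**Conclusion.** The point holds as two faults in the MRI paragraph of Statistical analysis.

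- **Contrast:** the test reads as a comparison of levels while the aim is change. Type I error is not inflated. The cost is a mismatch with the aim, unadjusted chance imbalance, and lost precision: at an assumed r of 0.7, baseline adjustment would leave about half (0.51) of the post-only variance.
- **Threshold:** p < 0.05 for a whole-brain test has no defined correction. Read as uncorrected and per voxel, at least one false region is almost certain; read as a corrected level, the rate is about 5%. The document does not settle which.

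Brain volume, resampling, smoothing and r are assumptions. The voxel counts are orders of magnitude, but the conclusion is not sensitive to them, since 100 independent tests already give 0.994. This should be settled before the MRI data are analysed. It ranks below a flaw in the primary analysis, because the SF-MPQ and CMSS comparisons are unaffected.

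**What to change.** Reconcile MRI data analysis, Statistical analysis and the Discussion in a few sentences:

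- **Contrast.** Compare arms on the post-treatment ALFF map, adjusted at each voxel for the participant's own baseline map. The team should confirm that its software accepts a map as a covariate. The alternative is a two-sample t test on post-minus-pre maps, stating that this loses precision relative to post-only if the pre-post correlation is below 0.5.
- **Threshold.** Declare significance only at a family-wise-error-corrected p < 0.05, for example cluster-level in SPM12 with a cluster-forming threshold stated in advance. Say whether the correction named under MRI data analysis is this step. Label any uncorrected maps descriptive.

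The cost is wording and some analyst time; no new data are needed. Fewer regions will be called significant, and baseline adjustment uses one degree of freedom at each voxel.
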